## **DRUG AND DEVICE INFORMATION**

*Investigators are encouraged to consult the UVM Medical Center Investigational Pharmacy Drug Service ([name]) prior to finalizing study drug/substance procedures.*

**Drug (s)**☐ **Not applicable**

Drug name – generic followed by brand name and common abbreviations. Availability – Source and pharmacology; vial or product sizes and supplier. If a placebo will be used, identify its contents and source. (attach investigational drug brochure)

IBT participants will receive buprenorphine/naloxone (Suboxone/Naloxone; BUP) sublingual tablets (Amneal Pharmaceuticals, Bridgewater, NJ), which will be obtained through the UVM Medical Center's Investigational Pharmacy. Buprenorphine is an FDA approved and widely used medication for treating opioid use disorder.

Preparation: Reconstitution instructions; preparation of a sterile product, compounded dosage form; mixing guidelines, including fluid and volume required. Identify who will prepare.

UVM Medical Center Outpatient Pharmacy at University Health Center

Storage and stability – for both intact and mixed products.

Administration – Describe acceptable routes and methods of administration and any associated risks of administration.

**Daily sublingual administration**

Toxicity – Accurate but concise listings of major toxicities. Rare toxicities, which may be severe, should be included by indicated incidence. Also adverse interactions with other drugs used in the protocol regimen as well as specific foods should be noted. Address significant drug or drug/food interactions in the consent form as well. List all with above details.

**No major toxicities**

Is it FDA approved: (include FDA IND Number)

1. in the dosage form specified? If no, provide justification for proposed use and source of the study drug in that form.

Y

2. for the route of administration specified? If no, provide justification for route and describe the method to accomplish.

Y

3. for the intended action?

Y

**Device (s)**☒ **Not applicable**

Device name and indications (attach investigational device brochure)

Is it FDA approved: (include FDA IDE Number)

1. for indication specified? If no, provide justification for proposed use and source of the device.

Risk assessment (non-significant/significant risk) - PI or sponsor needs to assess risk of a device based upon the use of the device with human subjects in a research environment.

**SUBJECT CHARACTERISTICS, IDENTIFICATION AND RECRUITMENT**

**Subject Selection:** Provide rationale for subject selection in terms of the scientific objectives and proposed study design.

Subjects will be adults with current opioid use disorder who are waitlisted for methadone or buprenorphine treatment

**Vulnerable Populations:** Explain the rationale for involvement of special classes of subjects, if any. Discuss what procedures or practices will be used in the protocol to minimize their susceptibility to undue influences and unnecessary risk (physical, psychological, etc.).

☒ **Not applicable**

**Number of Subjects:** What is the anticipated number of subjects to be enrolled at UVM/UVM Medical Center and in the case of a multi-center study, with UVM/UVM Medical Center as the lead, the total number of subjects for the entire study.

The anticipated number of subjects to be enrolled in the study is 100 (50 per experimental condition).

**Inclusion/Exclusion Criteria:** Eligibility and ineligibility criteria should be specific. Describe how eligibility will be determined and by whom. Changes to the eligibility criteria at a later phase of the research have the potential to invalidate the research.

Participants must be  $\geq 18$  years old, in good health, meet DSM-5 criteria for opioid use disorder and provide an opioid-positive urine at study intake. Consistent with our prior BUP studies, those with a significant psychiatric or medical illness that may interfere with consent or participation will be excluded, as will those who are pregnant or nursing. Those dependent on sedative-hypnotics will be excluded, due to the medical risks and notably low success rates with sedative-dependent opioid abusers (Stitzer & Chutuape, 1999). Intake information will be reviewed by the PI ([name]) and study physician ([name]), who will determine and document whether the participant is eligible and healthy to participate.

**Inclusion of Minorities and Women:** Describe efforts to include minorities and women. If either minorities or women are excluded, include a justification for the exclusion.

The study will include minorities and women. We will do all that we can to assure that women and minorities are represented in the research, including using a wide range of recruitment sources to ensure that information regarding this project reaches as diverse of a population as possible (e.g., flyers posted in multiple local neighborhoods, advertisements in the widely-distributed primary local newspaper as well as alternative local papers).

**Inclusion of Children:** Describe efforts to include children. Inclusion is required unless a clear and compelling rationale shows that inclusion is inappropriate with respect to the health of the subjects or that inclusion is inappropriate for the purpose of the study. If children are included, the description of the plan should include a rationale for selecting or excluding a specific age range of children. When included, the plan must also describe the expertise of the investigative team in working with children, the appropriateness of the available facilities to accommodate children, and the inclusion of a sufficient number of children to contribute to a meaningful analysis relative to the purpose of the study. **If children are excluded** then provide appropriate justification. Provide target accrual for this population.

Children will not be eligible for this study.

For protocols including the use of an investigational drug, indicate whether women of childbearing potential have been included and, if not, include appropriate justification.

N/A

If HIV testing is included specifically for research purposes explain how the test results will be protected against unauthorized disclosure. Include if the subjects are to be informed of the test results. If yes, include the process and provision for counseling. If no, a rationale for not informing the subjects should be included.

☒ **Not applicable**

**Recruitment:** Describe plans for identifying and recruitment of subjects. All recruitment materials (flyers, ads, letters, etc) need to be IRB approved prior to use.

The primary referral source will be distribution of an IRB-approved flyer to all CC waitlist individuals informing them about the study. Should this recruitment method ever become insufficient, we can also circulate ads throughout the larger community in order to reach additional patients on wait lists for BUP maintenance via OBOT. Additional sources will include self-referrals, drug abuse clinics, the Vermont State Alcohol and Drug Abuse Office, physicians, local mental health centers, a toll-free number, public service announcements, advertisements in local and alternative newspapers and flyers placed throughout the community. We have successfully recruited participants using these sources in prior studies (Dunn et al., 2008, 2010; [name] et al., 2009, 2013, 2015, 2016) and anticipate no difficulties gaining ready access to the sample needed.

Contact between participants and study staff will be initiated by the participants. Potential participants will respond to mailings or advertisements that contain a study description and the name and phone number of the Research Assistant. When potential participants call the Research Assistant, s/he will briefly describe the study and use a brief phone screen to make a preliminary determination about the potential participant's eligibility. Those who are interested in participating and appear to be eligible will be schedule for a longer intake screening that will begin with a full study description of study procedures. Those interested in undergoing study screening will then be provided with a copy of the consent form to read as we go over it with them. Risks and benefits of the study will be described. Potential participants will be asked to paraphrase the consent form and will be asked questions to determine their understanding of key elements of the informed consent. Potential participants who wish to proceed with the interview will be asked to sign the interview consent form and will be given a signed copy of his/her signed consent form.

## FINANCIAL CONSIDERATIONS

**Expense to Subject:** If the investigation involves the possibility of added expense to the subject (longer hospitalization, extra studies, etc.) indicate in detail how this will be handled. In cases where the FDA has authorized the drug or device company to charge the patient for the experimental drug or device, **a copy of the authorization letter from the FDA or sponsor must accompany the application. Final approval will not be granted until the IRB receives this documentation.**

There are very limited circumstances under which study participants may be responsible (either directly or via their insurance) for covering some study-related expenses. If the study participant or their insurer(s) will be billed for any portion of the research study, provide a justification as to why this is appropriate and acceptable. For example, if the study involves treatment that is documented standard of care and not investigational, state so. In these cases, the protocol and the consent should clearly define what is standard of care and what is research.

There are no expenses to the subject for any aspect of the study.

**Payment for participation:** Describe all plans to pay subjects, either in cash, a gift or gift certificate. Please note that all payments must be prorated throughout the life of the study. The IRB will not approve a study where there is only a lump sum payment at the end of the study because this can be considered coercive. The amount of payment must be justified. Clarify if subjects will be reimbursed for travel or other expenses.

☐ **Not applicable**

Participants will receive a \$30 gift certificate for completing each assessment (at intake and 4, 8, 12, 16, 20, and 24-week follow-up assessments).

**Collaborating Sites.** When research involving human subjects will take place at collaborating sites or other performance sites when UVM/UVM Medical Center is the lead site, the principal investigator must provide in this section a list of the collaborating sites and their Federalwide Assurance numbers when applicable. (agreements may be necessary)

☒ **Not applicable**

### INFORMED CONSENT

**Consent Procedures:** Describe the consent procedures to be followed, including the circumstances under which consent will be obtained, who will seek it, and the methods of documenting consent. Specify the form(s) that will be used e.g. consent (if multiple forms explain and place identifier on each form), assent form and/or HIPAA authorization (if PHI is included). These form(s) must accompany the protocol as an appendix or attachment.

**Note:** Only those individuals authorized to solicit consent may sign the consent form confirming that the prospective subject was provided the necessary information and that any questions asked were answered.

Only the site-PI ([name]) or trained, IRB-approved research staff will obtain informed consents for these studies. Informed consent will be initiated in a private office in the UHC building. Participants will be given unlimited time to decide if they wish to participate. The site-PI ([name]) and/or trained, IRB-approved research staff will be present and the PI will be continuously available to answer questions and explain all study procedures at any time.

**Information Withheld From Subjects:** Will any information about the research purpose and design be withheld from potential or participating subjects? If so, explain and justify the non-disclosure and describe plans for post-study debriefing.

☒ **Not applicable**

### Summary of important changes after Trial 1 commencement:

- 1.) Given changes in treatment availability in Vermont between the pilot and present studies, the inclusion criterion that participants be waitlisted for agonist maintenance was modified to include participants not currently receiving opioid agonist treatment.
- 2.) The target sample size was changed to 50 in concert with similar changes requested by funding agency for the parallel Trial 2.
- 3.) The Brief Pain Inventory (Cleeland, 1989, 1990; Keller et al., 2004) was added to the assessment battery.
- 4.) The opioid overdose educational module (below) was added to the intervention.
- 5.) HIV, HCV, and opioid overdose knowledge post-tests were added to the Week 4 assessment.
- 6.) Compensation for intake and monthly assessments was increased from \$30 to \$75 to facilitate timely recruitment.
- 7.) With the onset of the COVID-19 pandemic, the following modifications were made to the study protocol in situations where participants were at high-risk and/or currently experiencing COVID-19 symptoms: participants were permitted meet with study staff less frequently or remotely via phone or UVM's institutionally-supported Zoom platform to reduce the risk of COVID-19 transmission; biochemical samples may be omitted or collected using modified procedures to reduce risk of COVID transmission.

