## PURPOSE AND OBJECTIVES

**Purpose:** *The importance of the research and the potential knowledge to be gained should be explained in detail. Give background information.*

Opioid abuse and dependence have reached epidemic proportions in the US, resulting in premature death, criminal activity, and economic costs of over \$56 billion annually (Becker et al., 2008; Birnbaum et al., 2011; Clausen et al., 2009; Jones et al., 2013; Shah et al., 2008; SAMHSA, 2010; Wisniewski et al., 2008). The recent increases in opioid-related overdoses are particularly concerning, with 3- and 6-fold increases in overdose deaths related to prescription opioids and heroin, respectively, between 2001 and 2014 (CDC, 2015). Untreated opioid dependence has been associated with unprecedented outbreaks of HIV and Hepatitis C (Strathdee & Beyrer, 2015), and overdose deaths have now surpassed motor vehicle fatalities to become the country’s leading cause of injury death (CDC, 2016).

Treatment with agonist medications (e.g., methadone, buprenorphine) represents the most efficacious treatment for opioid dependence and dramatically reduces morbidity, mortality and spread of infectious disease (Schwartz et al., 2013; Stotts et al., 2009). However, demand for treatment far exceeds available capacity in many areas of the country (Friedmann et al., 2003; Harlow et al., 2013; [name], 2014), with **96% of states in the US having opioid abuse rates that exceed their medication-assisted treatment capacity** (Jones et al., 2015). The issue of insufficient treatment availability is especially urgent in rural areas (Paulozzi & Xi, 2008; Rintoul et al., 2011; Rosenblum et al., 2011; [name], 2014; Stein et al., 2015). The end result is that opioid-dependent individuals can remain on waitlists for months, during which they are at significant risk for illicit drug use, criminal activity, infectious disease, overdose and mortality (Chun et al., 2008; Clausen et al., 2009; Schwartz et al., 2009b). In one evaluation of survival rates among opioid-dependent individuals who received waitlist vs. immediate entry into methadone treatment, for example, **opioid treatment waitlists were associated with a 12-fold increase in risk of premature death** (Peles et al., 2013).

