randomized to the WLC condition will remain on the waitlist for their treatment of choice but complete the same monthly follow-up assessments with urinalysis, as described above for IBT participants. Participants will receive \$30 per assessment.

**For research involving survey, questionnaires, etc.:** Describe the setting and the mode of administering the instrument and the provisions for maintaining privacy and confidentiality. Include the duration, intervals of administration, and overall length of participation. (describe and attach all instruments)

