**Risks/Benefits:** Describe any potential or known risks. This includes physical, psychological, social, legal or other risks. Estimate the probability that given risk may occur, its severity and potential reversibility. If the study involves a placebo or washout period, the risks related to these must be addressed in both the protocol and consent. Describe the planned procedures for protecting against or minimizing potential risks and assess their likely effectiveness. Where appropriate, discuss plans for ensuring necessary medical or professional intervention in the event of adverse effects to the subjects. Discuss the potential benefits of the research to the subjects and others. Discuss why the risks to the subjects are reasonable in relation to the anticipated benefits to subjects and others. Discuss the importance of the knowledge gained or to be gained as a result of the proposed research and why the risks are reasonable in relation to the knowledge that reasonably may result. If there are no benefits state so.

Risks include breach of confidentiality and any side effects associated with the study medication (i.e., buprenorphine). Breach of confidentiality: Study data include medical and psychiatric histories and biological measures of alcohol and illicit drug use and pregnancy. The likelihood of a breach of confidentiality is low as we will take precautions to minimize this risk as described below under Adequacy of Protection against Risk.

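### As written, Trial 1 gives no emergency naloxone kit to either arm, although parallel Trial 2 gives one to every participant as a safety measure

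*Supplement*

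**What the plan says.** **Trial 1, background and eligibility.** The Purpose section says people can wait months for treatment, "during which they are at significant risk for illicit drug use, criminal activity, infectious disease, overdose and mortality". Participants must "meet DSM-5 criteria for opioid use disorder and provide an opioid-positive urine at study intake". After the trial began, the waitlist criterion was "modified to include participants not currently receiving opioid agonist treatment", and "The target sample size was changed to 50".

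**Trial 1, arms.** IBT consists of buprenorphine/naloxone tablets, nightly automated calls, random call-backs and HIV and hepatitis education. WLC participants "will remain on the waitlist for their treatment of choice but complete the same monthly follow-up assessments with urinalysis", and they are paid for each assessment.

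**Trial 1, safety text.** The Risks/Benefits section states: "Risks include breach of confidentiality and any side effects associated with the study medication (i.e., buprenorphine". Adverse events and serious adverse events are assessed at each clinic visit.

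**Trial 1, later changes on overdose.** There are two. Item 4: "The opioid overdose educational module (below) was added to the intervention". Item 5: "HIV, HCV, and opioid overdose knowledge post-tests were added to the Week 4 assessment".

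**Trial 2.** The Overdose prevention section describes an iPad module with knowledge tests and ends that paragraph by saying that overdoses and naloxone use will be asked about at every visit. The next paragraph gives all participants a two-dose naloxone kit as a safety measure in both arms. The Waitlist Control section repeats that WLC receives it.

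**The concern.** The two trials run in parallel, with the same two arms over 24 weeks, and the same investigators wrote both plans. In one they decided that everyone should hold rescue naloxone. In the other the text is silent, and no reason for the difference is given.

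What is at stake is participant safety. Everyone enters Trial 1 with an opioid-positive urine and, under the revised criterion, is not receiving agonist treatment. WLC participants may remain so for 24 weeks. The need is not confined to WLC: under Withdrawal Procedures, an IBT participant discharged for nonadherence must hand back all remaining buprenorphine. A knowledge module does not put naloxone in anyone's hands, and recording an overdose as an adverse event does not reverse it.

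**Working it through.** The plan states no figure on this point, so the check is mainly a comparison of texts.

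**1. Where naloxone appears in Trial 1.** Only as part of the buprenorphine/naloxone tablet (Procedures; Drug information) and in two reference titles. No rescue product is named for either arm.

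**2. Where overdose appears in Trial 1.** In the Purpose section, one reference title, and items 4 and 5 of the change list. It does not appear in the arm descriptions, the assessment battery, the nightly call content (drug and alcohol use, craving, withdrawal), or the risk, adverse-event and withdrawal text.

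**3. What item 4 can bring in.** The item refers to a module described below, but nothing about overdose follows in Trial 1's text. The only target shown is Trial 2's Overdose prevention section. The three elements there compare as follows:

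| Element | Where it stands in Trial 2 | Who receives it in Trial 2 | Named in Trial 1 items 4–5? |
|---|---|---|---|
| Education module and knowledge tests | Overdose prevention, first paragraph | Listed with the IBT components, including at crossover | Yes |
| Question on overdose and naloxone use | Last sentence of that same paragraph | Asked at each visit | No, but arguably covered by the cross-reference |
| Naloxone kit | Next paragraph, described as unrelated to the education outcome | All participants; WLC confirmed separately | No |

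Item 4 names the module and attaches it to the intervention. Trial 2 places the kit outside the module and outside the intervention. A reader who follows item 4 literally therefore has no instruction to hand out kits, least of all to WLC. The event question is a closer call, because it sits in the module's own paragraph.

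**4. Exposure without a study kit in WLC.** Inputs: revised target 50 (change list, item 2) and 24 weeks (Procedures). Assumptions: 50 is the total, which fits a reduction from 100 (50 per arm), and allocation remains 1:1.

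- WLC participants: 50 / 2 = 25
- Person-weeks: 25 × 24 = 600
- Person-years: 600 / 52.18 = 11.5

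This is an upper limit, since some participants may enter community treatment. The documents give no overdose rate, so no event count can be derived.

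**5. Size of the remedy.**

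- Kits: 50; doses at two per kit: 50 × 2 = 100
- Question at Weeks 4, 8, 12, 16, 20 and 24: 50 × 6 = at most 300 askings, 150 per arm

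**6. Why the recall window should match.** After induction, IBT has 12 scheduled visits (Weeks 2 to 24) plus 11 to 12 call-backs, or 23 to 24 contacts. WLC has 6. A question put at every visit would be asked about four times as often in IBT (24 / 6 = 4). Asking monthly, with one recall window, treats the arms alike.

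**The case against.** The strongest reply is that the cross-reference in item 4 imports the whole of Trial 2's Overdose prevention section: module, tests, question and kit all stand under that one heading. Other Trial 1 changes also move it towards Trial 2: the pain inventory, the sample size and the Week 4 post-tests. The change list is a one-line-per-item summary, the amendment behind it is not shown, and the body of the protocol predates the change, so silence there is expected. On this view the only defect is a loose cross-reference. Moreover, serious adverse events of any cause go to the investigator within 24 hours and to the ethics board within 5 days, and the state health department supports distributing kits to people at risk, so the lack of a study kit does not mean a lack of access.

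Much of this stands for the event question. A reader might infer that Trial 1 has no means of capturing overdoses. The documents do not support that: the question closes the paragraph to which item 4 most naturally points, and general adverse-event assessment exists.

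It is weaker for the kit. Item 4 names an educational module, not a section, and the investigators themselves describe the kit as something apart from that education. Alignment of the two trials makes adoption plausible but does not put the instruction in the text. Community access is possible, yet the investigators did not rely on it in Trial 2.

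**Conclusion.** The point holds for the kit: Trial 1 as written provides no emergency naloxone to either arm, while Trial 2 provides it to all. For the overdose question, the text is ambiguous rather than deficient.

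The size is up to 600 person-weeks (about 11.5 person-years) in WLC without a study-supplied kit, on the assumptions that 50 is the total and allocation is equal. That is exposure time, not a measure of harm.

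A reader might go further and infer that kits were withheld, that overdoses went unrecorded, or that the efficacy comparison is compromised. None of these follows. The documents show what the text provides, not what staff did; no between-arm overdose analysis is planned; and the primary endpoint, its test and its power are untouched. This is a change that should be made for participant safety, held with medium confidence because the amendment, instruments and consent pages are not shown.

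**What to change.** Amend Trial 1 in two places.

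1. **Kit.** Give every participant in both arms, at intake, the naloxone kit specified in Trial 2's Overdose prevention section, and say so in the Waitlist Control text.
2. **Item 4.** Replace the pointer with a statement of which Trial 2 overdose procedures apply and to which arm. State that the overdose and naloxone-use question is asked of both arms at Weeks 4, 8, 12, 16, 20 and 24, with the same recall window: since the previous monthly assessment, or since intake at Week 4.

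The cost is one amendment, about 50 kits and one short question at six existing assessments. In Trial 2 the health department supplies the kits; supply for Trial 1 is not stated and must be confirmed. The investigators have already judged for Trial 2 that kits in both arms do not confound the education outcomes. If the amendment behind item 4 already contains these provisions, only the wording of item 4 needs correcting.
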